## Sample size calculation

In the phase 2b, about 398 randomized patients, 199 patients in each group, will be included.

Assuming a true treatment difference in clinical failure rate of 10% for XAV-19 added to SoC therapy compared to placebo added to SoC therapy where a rate of 20% is expected, a sample size of 398 participants provides at least 80% power that the primary analysis will be statistically significant at the two-sided 5% significance level.

# General statistical considerations

## General Principes

### Confidence intervals and p-values

All applicable statistical tests will be 2-sided and will be performed using a 5% significance level.

No correction for multiple comparisons will be applied; all secondary objectives will be considered as exploratory and results were reported with only effect size estimates with their confidence intervals (CIs). All CIs presented will be 95%CI and 2-sided.

### Statistical software

Data will be analyzed using the SAS software (Version 9.4. SAS Institute Inc, Cary, NC, USA). Other package such as R software may be used if necessary.

## Protocol deviations

The following protocol deviations are pre-defined as major protocol violations with a direct bearing on primary outcome:

- Patients who did not respect treatment scheduled (i.e. for who treatment was not administrated or not entirely administrated)

- Patients who did not received the allocated treatment (treatment cross-over)

- Patients who did not verify all major inclusion criteria and all major non-inclusion criteria

- Patients lost to follow-up before day 15

- Patients who withdrew their consent before day 15

- Patients who had a respiratory failure before treatment administration

Protocol deviations will be identified and classified as major or minor in blind reviews before the database freezing. The number and % of patients with major and minor protocol deviations will be provided by treatment group, with details of the type of deviation. No formal statistical comparison will be done.

## Population definition

**Intent-to-treat (ITT) Population**: The ITT population will include all randomized patients, regardless of their eligibility and any protocol deviations, according to the treatment group to which they were assigned at randomization.

**Modified Intent-to-treat (mITT) Population**: The mITT population will include the ITT population but will exclude:

1. Patients who did not received treatment for any reason (withdrawn consent or investigator decision due to quick worsening of respiratory status before administration)
2. Patients with legal requirements (i.e. guardianship or trusteeship, < 18 years, no signed consent).

**Per-protocol (PP)**: The PP population will include the mITT population but will exclude:

1. Patients with treatment cross over, defined as receiving the other treatment
2. Patients with withdrawn consent between D1 and D15
3. Patients with major inclusion or non-inclusion criteria violation
4. Patients with major protocol deviations listed in section 3.2

The primary endpoint and the key secondary endpoints will be analysed on the ITT, mITT and the PP population.

The other secondary endpoints will be analysed on the mITT population only.

**Safety population**: The safety population will be included all randomized patients who have received the study treatment or placebo.

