**The other secondary endpoints are:**

1. National Early Warning Score (NEWS) assessed while hospitalized and on Day 15 and Day 29
2. Clinical status using the 8-point ordinal scale assessed daily until Day 29
3. Temperature and blood analysis between baseline and Day 15, and Day 29
4. Days of oxygen therapy over 29 days

PaO2 / FiO2 at baseline, Day 5, Day 8, Day 15, Day 29 if available

1. Days of non-invasive ventilation or high flow oxygen (if applicable) up to Day 29
2. Days of invasive mechanical ventilation/ECMO (if applicable) up to Day 29
3. Transfer in ICU
4. Hospital length of stay (in days)
5. All-cause mortality evaluated between baseline and Day 15 and between baseline and at Day 29 and at Day 60
6. Thrombotic events (peripheral venous, pulmonary, arterial)

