### Death

Mortality rate will be summarized by treatment group at day 15, day 29 and day 60.

Time data’s will be analyzed using a stratified log-rank test by treatment groups. Differences will be summarized with Kaplan-Meier curves and 95% confidence bounds.

The median time to event and 95% CI in each treatment group will be summarized and log rank test will be performed. Differences in time-to-event endpoints by treatment arm will be summarized with Kaplan-Meier curves. Number at risk, hazard ratio and log rank p-values will be presented on the figures.

Hazard ratio and 95%CI will be performed using Cox proportional hazards model.

28-day mortality may be summarized according to proportions by category and/or odds ratios with confidence intervals.

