### Safety Analyses

Safety endpoints include death through Day 60, SAEs and Grade 3 and 4 AEs.

Each AE will be counted once for a given subject and graded by severity and relationship to COVID-19 or study intervention. AEs will be coded using the current version of the Medical Dictionary for Regulatory Activities (MedDRA). AEs will be presented by system organ class, duration (in days). Adverse events leading to premature discontinuation from the study intervention and serious treatment-emergent AEs will be presented either in a table or a listing.

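### SAP 3.3 limits the mortality analysis to infused patients, although protocol 7.2.1 says efficacy data will also be shown for all randomised patients

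*Combined protocol and SAP*

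**What the plan says.** **Protocol.** Section 7.2.1 (phase 2b, efficacy analyses) says that efficacy data will be shown for the ITT population and for a treated population. Section 7.2.6 defines ITT as everyone randomised. Mortality is listed with the clinical severity objectives of phase 2b, separately from the safety objectives.

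**SAP, endpoint list (1.3).** The other secondary endpoints include "All-cause mortality evaluated between baseline and Day 15 and between baseline and at Day 29 and at Day 60".

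**SAP, populations (3.3).** For the composite outcomes, "The primary endpoint and the key secondary endpoints will be analysed on the ITT, mITT and the PP population". For everything else, "The other secondary endpoints will be analysed on the mITT population only". The mITT set removes any randomised patient who was not treated, whatever the reason. Two reasons are named: withdrawn consent, and "investigator decision due to quick worsening of respiratory status before administration". It also removes patients for legal reasons, such as guardianship or no signed consent.

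**SAP, mortality analysis (5.2, Death).** "Mortality rate will be summarized by treatment group at day 15, day 29 and day 60". Log-rank tests, Kaplan-Meier curves and a Cox model follow. No population is named, so the rule in 3.3 applies.

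**SAP, safety.** "Safety endpoints include death through Day 60, SAEs and Grade 3 and 4 AEs". However, "The safety population will be included all randomized patients who have received the study treatment or placebo", so this route does not bring back the non-infused patients either.

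**The concern.** Death is the endpoint for which an analysis of everyone randomised matters most to readers and is easiest to obtain. The SAP gives the composite outcomes an ITT analysis but not mortality.

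One of the named reasons for leaving the mITT set is a clinical event after randomisation that bears on the risk of death. SAP 2.4 allows randomisation on the day before infusion, and SAP 3.2 lists respiratory failure before treatment as a major deviation, so the plan itself expects worsening in that interval.

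At stake are a departure from what the protocol announced and the loss of a few deaths from the modelled comparison. An mITT result alone would also leave readers to trust, rather than see, that non-infusion did not differ between arms.

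**Working it through.** **1. The plan's own figure.** The documents give no figure for mortality or for non-infusion. The only related figure is the sample size in SAP 2.7: 20% versus 10% failure, two-sided 5%, 80% power, 1:1. With pooled variance and no continuity correction:

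n per arm = [1.960 × √(2 × 0.15 × 0.85) + 0.842 × √(0.20 × 0.80 + 0.10 × 0.90)]² / 0.10² = (0.990 + 0.421)² / 0.01 ≈ 199

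This gives 398 in total, as stated. Nothing below changes it.

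**2. Which analyses cover all randomised patients?**

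| Analysis in the SAP | Population | Includes non-infused patients? |
|---|---|---|
| Composite at D8, D15, D29 (5.2) | ITT, mITT, PP | Yes under ITT, but death is not separated out and follow-up stops at D29 |
| Mortality at D15, D29, D60 (5.2, Death) | mITT only, by 3.3 | No |
| Death as a safety endpoint, to D60 | Safety population | No |
| Flow diagram (Figure 1) | Allocated arms | Yes, as crude counts with no estimate or interval |

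The first row has a further uncertainty. SAP 5.1 words the composite event as occurring after infusion, so it is unclear how a death before infusion would count even under ITT.

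**3. How many deaths could be left out?** All rates here are assumptions.

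- Not infused: 1% to 3%. 398 × 0.01 ≈ 4 patients; 398 × 0.03 ≈ 12 patients.
- Mortality among them: 20% to 40%. 398 × 0.01 × 0.20 = 0.8 deaths; 398 × 0.03 × 0.40 = 4.8 deaths.
- Overall D60 mortality: 5% to 10%. 398 × 0.05 = 19.9 deaths; 398 × 0.10 = 39.8 deaths.

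Pairing the extremes, the share left out runs from 0.8 / 39.8 = 2% to 4.8 / 19.9 = 24%.

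**4. What would that do to the estimate?** Assumed counts: 10 deaths among infused patients on XAV-19 and 18 on placebo, 199 randomised per arm, and 4 non-infused patients who all die.

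| Non-infused deaths, XAV-19 / placebo | mITT risk ratio | ITT risk ratio |
|---|---|---|
| 2 / 2 | (10/197)/(18/197) = 0.556 | 12/20 = 0.600 |
| 3 / 1 | (10/196)/(18/198) = 0.561 | 13/19 = 0.684 |
| 4 / 0 | (10/195)/(18/199) = 0.567 | 14/18 = 0.778 |
| 0 / 4 | (10/199)/(18/195) = 0.544 | 10/22 = 0.455 |

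The mITT ratio barely moves and the ITT ratio does. With non-infusion independent of arm, the chance that all four fall in the same arm is about 2 × 0.5⁴ = 12.5%. The table does not show that mITT is biased. It shows that the two populations can give visibly different answers, and that the SAP would report only one of them.

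**The case against.** The case for leaving the SAP as it stands has substance.

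- **Bias.** A reader might infer that the mITT mortality estimate is biased, or is pushed about by chance imbalance in the exclusions. The documents do not support that. The trial is double-blind, SAP 2.4 keeps the gap to about one day, and protocol 6.2.1 asks for same-day dosing where possible. Patients never infused cannot respond to the product, so their removal should not depend on arm. Step 4 shows a stable mITT ratio. This part of the objection stands.
- **No comparison at all.** A reader might also infer that deaths among all randomised patients would go unreported. That is too strong. The flow diagram gives deaths by allocated arm over 60 days, and death is a component of the ITT composites to D29. What is missing is a modelled comparison of mortality itself, at any time point.
- **Everyone who worsened is dropped.** That is not what SAP 3.3 says. A patient who worsened but was still infused stays in mITT. Some of those removed leave for consent or legal reasons and need not be at high risk of death. Death before infusion is not named; it falls under the general wording.
- **Weight.** SAP 3.1 treats all secondary objectives as exploratory, reported as estimates with intervals. No confirmatory claim rests on this choice.

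These points limit the severity. They do not answer the conflict with protocol 7.2.1, nor do they explain why mortality gets less than the composite outcomes.

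**Conclusion.** The point holds as a conflict between protocol and SAP, and it is minor. The protocol announces efficacy results on all randomised patients. The SAP confines mortality at D15, D29 and D60 to infused patients, and its safety population does not fill the gap. The exclusion depends in part on prognosis after randomisation.

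On the assumptions in step 3, about 1 to 5 deaths would be left out, against 20 to 40 overall. The true number could be close to zero, because nothing in the documents fixes the non-infusion rate. No direction of bias is claimed, and the sample size and primary analysis are unaffected.

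**What to change.** Reconcile SAP 3.3 with protocol 7.2.1 by adding: *All-cause mortality at D15, D29 and D60 is analysed on the ITT population, counted from randomisation; the mITT result is supportive.*

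The definition of time to death in SAP 5.1, which starts at D1, should be aligned, since randomisation may fall on the day before infusion.

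The cost is one more run of an analysis already programmed. Vital status must also be sought for non-infused patients who have not refused follow-up; the protocol already schedules a Day 60 contact. Where consent was withdrawn, vital status may stay unknown, and the number of such patients should be reported by arm.

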# Trial population

## Screening data

The number of screened patients (patients with sign consent), number of randomized patients and the reason for non-randomization will be reported for overall population according to consort flow diagram (figure 1) compliant with the CONSORT 2010 standard.

## Withdrawal/ Lost to Follow-up

The level of withdrawal will be tabulate and classified as:

- Withdraw consent before infusion or during follow-up

- Lost to follow-up at any time during study

- Withdraw due to investigator decisions (reasons should be detailed)

The timing of withdrawal and reasons for withdrawal will be provided by treatment group according to consort flow diagram (figure 1) compliant with the CONSORT 2010 standard.

**Figure 1. Flow of participation in the POLYCOR trial.**

Screened patients (**n=**)

Excluded (**n=**)

Withdraw consent before randomisation (n=) *

Degradation / improvement of clinical status (n=)

Other reasons (n=)*

***Enrollment***

Randomized (**n=**)

***Allocation***

Allocated to XAV-19 + Soc arm (**n=)**

Received allocated intervention (n=)

Did not receive allocated intervention (n=)

Allocated to Placebo + Soc arm (**n=)**

Received allocated intervention (n=)

Did not receive allocated intervention (n=)

Died (n=) or completed follow-up (**n=**)

-lost to follow-up (n=)

-withdrawn consent (n=)

-Other reasons (n=)*

Died (n=) or completed follow-up (**n=**)

-lost to follow-up (n=)

-withdrawn consent (n=)†

-Other reasons (n=)*

***60-day Follow-up***

***Primary Efficacy Analysis***

Analyzed (**n=**)

-excluded (n=)*

Analyzed (**n=**)

-excluded (n=)*

**Table 1. Baseline patient’s characteristics**

| **Characteristics** | **Xav19 + Soc** (N=) | **Placebo + Soc** (N=) |
| --- | --- | --- |
| **Baseline demographics and medical history** |  |  |
| **Age** (in years) |  |  |
| Mean (SD) |  |  |
| Category N (%) |  |  |
| <=50 |  |  |
| > 50-65 |  |  |
| > 65-75  > 75 |  |  |
| **Sex (N (%))** |  |  |
| Women |  |  |
| **Height** mean (SD) |  |  |
| **Weight** mean (SD) |  |  |
| **BMI**  Mean (SD)  Category N (%)  <30  30-34  35-40  >40 |  |  |
| **Medical history** |  |  |
| Hypertension  Other chronic cardiovascular disease |  |  |
| Diabetes |  |  |
| COPD  Other chronic lung disease, including asthma |  |  |
| Chronic kidney disease, including dialysis  Cancer  Solid organ transplant  HIV infection  Other immunosuppressive condition, based on investigator’s assessment |  |  |
|  |  |  |
| **Duration of symptoms before enrollment** |  |  |
| Mean (SD) |  |  |
| ≤ 6 days (%) |  |  |
| 7-10 days |  |  |
| 11-14 days  **Concomitant treatment** |  |  |
|  |  |  |
| **NEWS score** N (%)  2-4 |  |  |
| 5-6 |  |  |
| 7 and more  **SpO2 Mean ( SD)**  **O2 supplement**  < 4L/min  ≥4L/min  Variant’s type  COVID serology if possible |  |  |

# Statistical methods

Data on primary and secondary efficacy/safety outcomes will be performed by academic statisticians.

## Outcome definitions

### Baseline Value

For efficacy assessments, the baseline value will be defined as the value obtained at D1 before infusion.

For safety assessments, the baseline value will be defined as the last value obtained before infusion. This value may have been taken during the screening visit (i.e. up to 2 days before) or D1.

### Clinical status: WHO 8 point ordinal scale

The ordinal scale of the clinical status will be assessed at each study visit.

Each day, the worse score of the day will be recorded.

Reference: <https://www.who.int/blueprint/priority-diseases/key-action/COVID-19_Treatment_Trial_Design_Master_Protocol_synopsis_Final_18022020.pdf>

[figure not shown]

### Respiratory failure or death

Respiratory failure is defined by a requirement of low oxygen delivery device and a flow ≥ 10 L / min with reservoir, or high-flow oxygen devices or noninvasive ventilation, or invasive mechanical ventilation or death after infusion of treatment. This is related to a value of 5, 6, 7, or 8 on the clinical status 8-point ordinal scale.

Respiratory failure will be evaluated between baseline and day 15 (primary objective), between baseline and day 8, and between baseline and day 29 (key secondary objectives).

The primary outcome measures the number of patients who had at least one respiratory failure after baseline (D1 before infusion).

The time to respiratory failure will be defined as the elapsed time (in days) from baseline (on Day 1) to the first day at which a subject reaches any respiratory failure.

### NEWS score (version 2)

NEWS score is an early warning score developed for monitoring hospital in-patients over time using repeated measures.

NEWS has demonstrated an ability to discriminate subjects at risk of poor outcomes.

This score is based on 7 clinical parameters.

Reference: https://www.cebm.net/covid-19/should-we-use-the-news-or-news2-score-when-assessing-patients-with-possible-covid-19-in-primary-care.

The NEWS is based on a simple aggregate scoring system in which a score is allocated to physiological measurements. Six simple physiological parameters form the basis of the scoring system:

- respiration rate
- oxygen saturation
- systolic blood pressure
- pulse rate
- level of consciousness or new confusion
- temperature.

The score is then aggregated and uplifted by 2 points for people requiring supplemental oxygen to maintain their recommended oxygen saturation.

[figure not shown]

This should be evaluated at the first assessment of a given study day and prior to administration of study product. The 7 parameters can be obtained from the hospital chart using the last measurement prior to the time of assessment and a numeric score given for each parameter (e.g., a RR of 9 is one point, oxygen saturation of 92 is two points).

This score takes into account hypercapnic respiratory failure over time, using scale 2 for Sp02.

### Time to Discharge or NEWS of ≤ 2 over 29 days

The time to discharge or NEWS of ≤ 2 will be defined as the elapsed time (in days) from baseline to the earliest day at which either of the following occurs:

• Discharge from hospital

• Reported NEWS of ≤ 2

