**Clinical severity**:

a) National Early Warning Score (NEWS) over 29 days:

- Change from baseline to Day 3, 5, 8, 15 and 29

- Time to discharge or a NEWS <=2 and maintained for 24 hours

b) 8-point ordinal scale over 29 days

- Time to improvement of one category from baseline

- Time to respiratory failure

- Mean change in ordinal scale from baseline to Day 3, 5, 8, 15 and 29

- Percentage of subjects reporting each severity rating on an 8-point ordinal scale at Day15

c) Improvement of clinical and biological parameters over Day 15

d) Oxygenation

- Duration of oxygen therapy over 29 days

- Time to weaning in supplemental oxygen

- Proportion without O2 requirement at D8, D15 and D29

e) Non-invasive ventilation, high-flow oxygen

- Non-invasive ventilation/high flow oxygen use up to Day 29

- Incidence and duration of non-invasive ventilation or high flow oxygen use during the study

- Time to first day with non-invasive ventilation/high flow oxygen

f) Invasive mechanical ventilation / Extra Corporeal Membrane Oxygenation (ECMO)

- Ventilator / ECMO use up to Day 29

- Incidence and duration of new mechanical ventilation or ECMO use during the study

- Time to first day with Invasive Mechanical Ventilation / extracorporeal membrane oxygenation

g) Transfer to ICU by Day 29

h) Hospitalization

- Hospital length of stay (in days)

i) Mortality

- Mortality rate at day 15 and at Day 29 and at Day 60

j) Thrombotic events

- Cumulative incidence of thrombotic events: venous, pulmonary embolism, arterial thrombotic events.

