### Secondary outcomes analyses

### NEWS score

The median time to discharge or to a NEWS ≤ 2 will be summarized by treatment group.

Time to discharge or to a NEWS ≤ 2 will be compared between groups using Fine & Gray method to take into account competing risk (death).

The mean, standard deviation (SD), median, IQR, minimum, and maximum NEWS at baseline and each study visit will be presented by treatment arm as well as change from baseline.

Change in NEWS score at specific time points will be summarized by proportions (e.g., proportion who have a 1-, 2-, 3-, or 4-point improvement or 1-, 2-, 3-, 4-point worsening).

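### The SAP's working definition counts any single NEWS of 2 or less as the event, while the protocol and SAP objectives require it to be maintained for 24 hours

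*Combined protocol and SAP*

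**What the plan says.** **Objective.** The protocol (Phase 2b secondary objectives, Clinical severity, item a) and SAP 1.2 use the same words: "Time to discharge or a NEWS <=2 and maintained for 24 hours".

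**Working definition.** SAP 5.1 (Time to Discharge or NEWS of ≤ 2 over 29 days) defines the time as the "elapsed time (in days) from baseline to the earliest day at which either of the following occurs". The two listed events are discharge and "Reported NEWS of ≤ 2". No duration or confirming reading is asked for.

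**Analysis.** SAP 5.2 (NEWS score) says "Time to discharge or to a NEWS ≤ 2 will be compared between groups using Fine & Gray method", with death as the competing risk and again no duration.

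**Baseline and scoring.** For efficacy, "the baseline value will be defined as the value obtained at D1 before infusion". On timing of the NEWS, SAP 5.1 says "This should be evaluated at the first assessment of a given study day and prior to administration of study product". Oxygen adds points: "The score is then aggregated and uplifted by 2 points for people requiring supplemental oxygen to maintain their recommended oxygen saturation". SAP 2.2 requires every patient to be on oxygen at screening.

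**Status.** SAP 3.1 makes all secondary objectives exploratory, reported as effect estimates with confidence intervals. SAP 3.3 assigns this endpoint to the mITT population.

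**The concern.** The SAP disagrees with itself and with the protocol about what the event is. Because only the earliest qualifying day counts, a patient who scores 2 once and then deteriorates is recorded as having improved, and nothing later undoes that. The result would be reported under an objective that the analysis does not measure.

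A second gap concerns the start of the clock. SAP 5.1 (Respiratory failure or death) limits the primary outcome to events after the pre-infusion baseline. The NEWS endpoint has no such limit, and no rule covers patients whose baseline NEWS is already 2 or less. An event at time 0 precedes treatment and cannot carry information about it.

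**Working it through.** **1. Planning figure.** The only phase 2b planning figure is the primary sample size. For 20% against 10%, two-sided 5%, 80% power, 1:1 allocation and pooled variance without continuity correction, the two-proportion formula gives 199 per arm, 398 in total, with power 0.800. This reproduces SAP 2.7. Nothing is planned for the NEWS endpoint, so no stated figure changes.

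**2. The definitions side by side.**

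| Place | NEWS component | 24-hour condition |
|---|---|---|
| Protocol, Phase 2b secondary objectives | ≤ 2 | yes |
| SAP 1.2 | ≤ 2 | yes |
| SAP 5.1 definition | ≤ 2, earliest day | no |
| SAP 5.2 analysis | ≤ 2 | no |

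The missing-data rules in SAP 5.4 do not restore the condition.

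**3. Baseline arithmetic.** On oxygen with 0 points on the six other parameters, NEWS = 2 + 0 = 2, which meets the SAP 5.1 event on the pre-infusion Day 1 reading. On oxygen with a saturation of 92, which SAP 5.1 scores as 2 points, NEWS is at least 2 + 2 = 4 and does not meet it. For a patient on oxygen, this route therefore needs a NEWS of exactly 2.

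**4. Chance of a false event from transient readings (illustration).** Assume independent daily readings, each with chance p of an isolated NEWS ≤ 2, over k days before true recovery. With a single reading the chance is 1 − (1 − p)^k. The last column requires two consecutive daily readings as a stand-in for 24 hours.

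| p | k | Single reading | Two consecutive |
|---|---|---|---|
| 0.05 | 3 | 1 − 0.95³ = 14% | 0.5% |
| 0.10 | 5 | 1 − 0.90⁵ = 41% | 3.7% |
| 0.20 | 7 | 1 − 0.80⁷ = 79% | 19% |

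The documents give neither p nor k.

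**5. Effect on the ratio (illustration).** Assume a true ratio of 1.40, a 9% daily control event rate, and transient readings with daily chance t unrelated to treatment. With daily scoring the observed ratio is about (1.40 × 0.09 + t) / (0.09 + t):

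- t = 0.03: 0.156 / 0.120 = 1.30
- t = 0.05: 0.176 / 0.140 = 1.26

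Simulation with 199 per arm over 28 days (Cox, no deaths) gives about 1.29 and 1.26. If NEWS is read only at the scheduled visits, so that t applies per visit, it gives about 1.36 and 1.32. No baseline events are included in these figures.

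**The case against.** The strongest reply is that this is a wording slip in one exploratory secondary endpoint, applied alike to both blinded arms, with no bearing on the primary or key secondary analyses. That sets the size of the point but does not remove it: the two written definitions give different event times, and SAP 3.1 says it is the effect estimate that will be reported.

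Three stronger readings are tempting, and the documents do not support them.

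- *Dropping the 24-hour condition is what lets patients have the event at baseline.* It is not. A stable baseline NEWS of 2 also satisfies the objective's wording, at or near time 0. This is a separate gap that the objective shares.
- *The baseline class 2-4 in SAP Table 1 and SAP 5.3 shows that such patients are expected.* It starts at 2 because 2 is the lowest possible score for a patient on oxygen. It does not show that anyone scores exactly 2.
- *The endpoint loses a known amount of power.* The true ratio, the event rate and the frequency of transient readings are all assumed. If treatment raised transient readings by the same factor of 1.40, the ratio would be 1.40 × (0.09 + t) / (0.09 + t) = 1.40, with no dilution. The illustration also uses Cox without deaths, whereas SAP 5.2 specifies Fine & Gray.

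The objection on assessment frequency also stands. The Phase 2b schedule has no NEWS row, and its visits are D1, D2, D3, D5, D8, D15 and D29. SAP 1.3 has NEWS assessed while hospitalized and on D15 and D29, so daily scoring is possible but not stated.

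**Conclusion.** The inconsistency is real, and no other text resolves it. SAP 5.1 and 5.2, followed as written, measure time to discharge or a first low NEWS, whereas the objective asks for a sustained one. The absence of a post-baseline limit is a second, narrower gap; the number of patients affected is unknown.

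The expected direction is earlier event times and probable dilution of the contrast. The fall from 1.40 to about 1.29-1.26 (daily scoring) or 1.36-1.32 (visit-only scoring) shows what a 3-5% chance of a transient reading could do under the stated assumptions. It is not an estimate for this trial. The primary and key secondary analyses are unaffected. The definition should be corrected, and settled before the Day 29 unblinding in SAP 2.6, because choosing between two written definitions afterwards could depend on the data.

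**What to change.** In SAP 5.1 and 5.2, define the event as: *discharge, or NEWS ≤ 2 maintained for at least 24 hours, based on assessments after the D1 infusion*.

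Name the confirming reading: the daily hospital-chart NEWS while the patient is hospitalized, otherwise the next available score. SAP 5.1 already allows the parameters to be taken from the chart.

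Keep all mITT patients in the analysis, as SAP 3.3 requires. Report the number with baseline NEWS ≤ 2 by arm. Add a sensitivity analysis in which these patients reach the event only by discharge, since a baseline score of 2 that persists after infusion would still qualify under the new wording. Using that rule as the main analysis, or leaving these patients out, would go beyond the stated objective or depart from the mITT set.

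**Cost.** A short SAP change and a little programming. Some events will be dated later. Where NEWS is recorded only at visits, the delay can be a full visit interval: 7 days from D8 to D15, or 14 days from D15 to D29.
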